### Safety Monitoring

#### Adverse Event

An adverse event (AE) will be considered as any untoward medical occurrence in a subject that is new in onset or an exacerbation of a preexisting condition, whether related to study product or procedures or not. However, medical occurrence resulting from a pretreatment AE (ie, any medical occurrence that occurs after informed consent but before the start of the intervention) will be considered as medical history and only recorded as an AE if it worsens during the study. Similarly, a medical occurrence resulting from preexisting medical condition (ie, events that occur with comparable frequency and severity to the subject’s baseline condition) is reported as medical history and not AE. Relatedness—the likelihood that an AE is related to the study product or study procedure—of an AE is defined in Table 3. An AE will be recorded only once, with the most extreme severity:

Mild: awareness of symptoms that require minimal or no treatment and do not interfere with daily activityModerate: discomfort or low level of interference that is enough to interfere with but not prevent daily activitySevere: interrupted or unable to perform usual daily activity; usually requires treatment

**Table 3 table3:** Relatedness of adverse events.

Relatedness	Definition
Not related	AE^a^ is clearly due to an alternative cause, even if this cannot be definitely identified. Alternative causes include diseases and environmental factors.
Unlikely	Connection between AE and the study product or procedure is unlikely: AE has a relationship in time to the study product or procedure Alternative cause (eg, disease or environmental factor) is the most likely explanation, even if this cannot be identified
Possibly	Connection between AE and the study product or procedure cannot be ruled out with certainty: AE has a relationship in time to the study product or procedure Alternative cause (eg, disease or environmental factor) seems likely or possible or there is significant uncertainty about the cause of the AE
Probably	There is a high degree of certainty that the AE is related to the study product or procedure: AE has a relationship in time to the study product or procedure Possible alternative cause may be present AE disappears or decreases on withdrawal or reduction of study product or procedure (if performed)
Definitely	AE is clearly related to the study product or procedure: There is a strong relationship in time Alternative cause is unlikely AE disappears or decreases on withdrawal or reduction of study product or procedure (if performed)

^a^AE: adverse event.

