**Methods:**

The study is a 2-arm superiority randomized controlled trial. Clusters in this study are infant and junior schools in Indonesia and Nigeria. The study aims to recruit 20 schools with children aged 6 to 9 years in each country. At baseline, children in both intervention and control schools will answer a questionnaire and have their clinical oral health assessed using the Simplified Oral Hygiene Index (OHI) and Decayed Missing and Filled Teeth index. Children in the intervention schools will then take part in a structured 21-day Brush Day & Night intervention. Children in the control schools will be provided with free toothpaste and toothbrushes but will not receive the 21-day intervention. The questionnaires and OHI assessments are repeated after the 21-day program is completed and again 8 weeks later and 24 weeks later for all participating children. Parents/carers/guardians of all children will sign the informed consent and complete questionnaires on their own experience and attitudes toward oral health and toothbrushing routine at each of the four times points (baseline, 21 days, 8 weeks, and 24 weeks). The study will be conducted by the national dental associations of Indonesia and Nigeria and was approved by the ethics committees of both countries.

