### Study Design

This study is a 2-arm, superiority cluster randomized trial. Clusters in this study are infant and junior schools in Indonesia and Nigeria. Schools will be matched into pairs by location and then randomized to intervention and control groups using a randomization table.

The study will look to recruit children aged 6 to 9 years in school grades 1, 2, and 3 to participate in the study. Children who assent to take part in the study (see Multimedia Appendix 2 for form), meet the selection criteria, and have the informed consent of their parents (see Multimedia Appendix 3 for form) will be enrolled in the study. The study flowchart is shown in Figure 1.

The T0 (baseline), T0+21 (end of 21-day intervention), T1 (8 weeks after the end of the intervention), and T2 (24 weeks after the end of the intervention) data collection time points will consist of questionnaire completion and a clinical assessment of plaque level evaluation using the Simplified Oral Hygiene Index (OHI-S) and an additional caries evaluation at T0 and T2 using the Decayed, Missing, and Filled Teeth index (DMFT). For the control group, the same flowchart will be followed, but the “Start 21-day BDN program/Finish 21-day BDN program” is replaced by only providing toothpaste and toothbrushes to school children.

The delivery of the intervention program relies on Unilever materials including toothpaste and toothbrushes as well as all the necessary educational materials. These materials are produced and delivered by Unilever locally. Translations of the materials to a local language will be completed if necessary. Toothpaste provided in Indonesia will be a commercially available and marketed product manufactured by Unilever Indonesia containing 1450 ppm fluoride as 1.12% sodium monofluorophosphate in a chalk base (Pepsodent Anti-Cavity or similar). In Nigeria, a commercially available and marketed toothpaste sold by Unilever Nigeria containing 1450 ppm fluoride (0.32% sodium fluoride) in a silica abrasive (Pepsodent Cavity Fighter Gel or similar) will be provided.

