#### Serious Adverse Event

A serious adverse event (SAE) is an AE that results in any of the following outcomes: death, life-threatening event, in-patient hospitalization, persistent or significant disability/incapacity. Any other important medical event may be considered an SAE when the event may jeopardize the subject and may require medical or surgical intervention to prevent one of the outcomes listed. A stable preexisting condition is not an AE, and hospitalization for elective treatment (eg, cosmetic or dental procedure) of a preexisting condition that did not worsen from baseline is not an SAE.

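### The pretreatment rule files a new, non-worsening harm from the baseline examination as medical history, although the adverse event definition covers study procedures

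*Protocol article*

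**What the plan says.** The Adverse Event section opens with a broad definition. It takes in untoward medical occurrences that are new or are exacerbations, "whether related to study product or procedures or not". Relatedness is likewise "the likelihood that an AE is related to the study product or study procedure", so procedures count alongside the toothpaste and toothbrush.

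The same section then sets a pretreatment rule. It describes a pretreatment AE as "any medical occurrence that occurs after informed consent but before the start of the intervention". What results from one "will be considered as medical history and only recorded as an AE if it worsens during the study". A separate sentence deals with preexisting conditions that recur with comparable frequency and severity; these are also medical history.

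The Serious Adverse Event section builds on the AE definition: "A serious adverse event (SAE) is an AE that results in any of the following outcomes". It adds a residual clause: "Any other important medical event may be considered an SAE when the event may jeopardize the subject". Under Reporting of Adverse Events, an SAE goes to FDI within 24 hours of the local coordinator learning of it. Under Follow-Up of Adverse Events, the minimum report to the ethics committee concerns unexpected SAEs that may be related to product or procedure.

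On timing, the Methods paragraph of the abstract has children in both arms examined at baseline, after which the intervention schools begin the program. Study Design makes parental consent a condition of enrollment. For control schools it keeps the same flowchart, except that the program's start and finish "is replaced by only providing toothpaste and toothbrushes to school children".

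**The concern.** Two statements in one section pull against each other. The definition says that harm from a study procedure can be an AE. The pretreatment rule removes occurrences from a window that contains one of the study's own procedures, the T0 oral examination. For a child injured or made ill by that examination who then recovers, both statements cannot be applied.

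At stake is whether procedure-related harm in 6- to 9-year-old children at the first of four examination visits is recorded, and whether a serious event of that kind triggers prompt reporting. Such an event could go unreported without anyone departing from the protocol.

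A smaller matter is that the window closes at the start of the intervention, and the safety text does not say what that means in a school that does not receive the program.

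**Working it through.** No plan figure has to be reproduced, because the point turns on wording. The check sets the provisions side by side.

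1. **Is the T0 examination a study procedure?** Yes. Table 1 schedules the Simplified Oral Hygiene Index (OHI-S) and the Decayed, Missing, and Filled Teeth index (DMFT) at baseline, and the schedule is the same for both groups.

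2. **Does it fall inside the pretreatment window?** Consent is a condition of enrollment (Study Design), so by inference it precedes T0. The abstract places the program after the baseline assessment. The order is consent, then T0 examination, then start of intervention. The flowchart figure is not available, so this order is taken from the text.

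3. **How is a new harm from the T0 examination classified?**

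| Course of the event | Status under the Adverse Event section |
|---|---|
| New at T0, worsens during the study | Recorded as an AE, and may then be an SAE |
| New at T0, resolves or stays stable | Medical history, not recorded as an AE |
| New at a later examination (T0+21, T1, T2) | AE; the pretreatment rule does not reach it |

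The second row is the conflict. The opening definition and the relatedness scale would both include that event.

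4. **Does the gap carry into serious events?** An SAE must first be an AE. An event in the second row that led to hospitalization and then resolved does not meet the main SAE definition, so the 24-hour report does not follow from it. The ethics committee minimum is also framed in terms of SAEs and inherits the gap. The residual clause on other important medical events refers to an event rather than an AE and could rescue some cases, but its wording leaves that to judgment.

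5. **How much examination activity is affected?** From Table 1, T0 accounts for 1 of 4 OHI-S examinations (1/4 = 25%) and 1 of 2 DMFT examinations (1/2 = 50%). Selection of Schools gives 20 schools per country and about 30 children per class. With three grades, and assuming one class per grade, 20 × 3 × 30 = 1,800 children per country would be examined at T0. These figures count examinations and children. They do not count harms.

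6. **What is the control-arm anchor?** Study Design puts product provision where the program start stands, which gives control schools a natural equivalent date. The Adverse Event section does not state that equivalence.

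**The case against.** The strongest reply is textual. Read literally, the rule does not reclassify the pretreatment event itself. It concerns a medical occurrence resulting from a pretreatment AE, and so calls the first event an AE. On that reading a serious T0 injury could still be an SAE. The wording is loose enough to allow the argument. But the same sentence says that recording as an AE happens only on worsening, which would be pointless if the event were already an AE. The reading is strained, and a coordinator could not be expected to apply it.

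Several stronger inferences might tempt a reader, and the documents do not support them:

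- **That T0 harm can never become an AE or SAE.** The worsening exception and the discretionary SAE clause both leave a route.
- **That control schools have no start date at all.** It is true that "Children in the control schools will be provided with free toothpaste and toothbrushes but will not receive the 21-day intervention", but Study Design substitutes product provision for the program start. Only an explicit statement in the safety text is lacking.
- **That the arms have different AE windows, so that counts are not comparable.** The T0 examination is the same in both arms, and with the Study Design substitution the window closes at the corresponding step in each. Table 2 lists no between-arm AE comparison among the five objectives.
- **That the examination counts measure missed harm.** No event rate is given for a plaque and caries examination, and few events may be involved.

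It also stands that this is a condensed article, and that coordinator instructions may say more. That does not settle the matter, because the objection is to a rule the article states, not to one it omits.

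**Conclusion.** The point holds in a limited form. As written, the pretreatment rule conflicts with the AE definition and the relatedness scale for one class of event: a new harm caused by the T0 examination that does not later worsen. Such an event is not recorded as an AE and falls outside the main SAE definition and the 24-hour report, subject to the discretionary clause.

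The effect is confined to T0 and applies equally to both arms. Its frequency cannot be estimated from the documents. No efficacy analysis is touched. The unstated control-arm anchor is minor.

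The conclusion rests on two assumptions: that consent precedes the T0 examination, as the enrollment condition implies, and that the worsening condition is read in its ordinary sense. The conflict should be corrected, because it lies in the safety definitions of a trial in children and takes little to remove.

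**What to change.** Rewrite the pretreatment sentence so that AE and SAE recording opens in both arms at the first study procedure, the T0 examination. New events from that point on are then AEs, and the AE, SAE and relatedness definitions agree. Events between consent and that procedure can remain medical history unless they worsen.

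Keep the separate sentence on preexisting conditions of comparable frequency and severity. Otherwise ordinary recurrences after T0 would be turned into AEs.

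Because T0 occurs in every school, this wording also removes the need for a separate control-arm anchor.

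The cost is one sentence in the definition, a matching line in the coordinator instructions, and a few more events to log. The article describes the study as ongoing, with AEs submitted at its end, so events around T0 could still be reviewed under the corrected rule where site records allow.

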#### Serious Adverse Event

A serious adverse event (SAE) is an AE that results in any of the following outcomes: death, life-threatening event, in-patient hospitalization, persistent or significant disability/incapacity. Any other important medical event may be considered an SAE when the event may jeopardize the subject and may require medical or surgical intervention to prevent one of the outcomes listed. A stable preexisting condition is not an AE, and hospitalization for elective treatment (eg, cosmetic or dental procedure) of a preexisting condition that did not worsen from baseline is not an SAE.

#### Reporting of Adverse Events

AEs will be monitored, reported, and followed up to the public health authorities. All AEs will be recorded and submitted to the FDI global team at the end of the study. The LSC will maintain source documents to fully record all AEs.

Additionally, SAEs and clusters of AEs that may affect the safety or continued participation of participants in the study will be reported immediately using a more detailed form. An SAE will be reported to FDI within 24 hours of the LSC becoming aware of the event.

#### Follow-Up of Adverse Events

If an AE is ongoing at the end of the study, follow-up will be performed until the AE has resolved, unless decided and agreed that no further follow-up will be necessary. Follow-up may take the form of subject visits, referral to another specialist, site telephone calls to the subject, or letters from the treating physician. For expedited AEs, if applicable, the LSC will submit follow-up reports. The LSC will comply with the specific reporting requirements of the ethics committee, reporting as a minimum any serious unexpected adverse reaction that is an unexpected SAE that may be related to study product or procedure.

## Results

This protocol is being retrospectively published with the information shared with the two participating countries on January 19, 2019. In the meantime, the trial was set up, and the study is ongoing. Recruitment of schools and participants started in Indonesia in February 2018 and in Nigeria in April 2018 for the first part of the study, which concluded in Indonesia in September 2018 and in Nigeria in November 2018. The second part of the study (the second half of the schools) started in November 2018 in Indonesia and December 2018 in Nigeria. We expect to collect all the data during 2019 and publish findings from the study by March 2020.

## Discussion

This new study will include both intervention and control schools and children and ensure that evaluations (knowledge, behavior, plaque levels, and dental caries) are made within a clearly defined time window to facilitate data analysis.

Children in the control group will not receive the 21-day school program intervention. This will allow a full evaluation of the benefit of the intervention. The OHI-S will be used to score plaque. This is a 4-point scale and hence will be more discriminatory than the 2-point (visible plaque index) scale used previously. This is the first time that the 21-day BDN program has been evaluated in a study with a set of control schools. The impact of such a program on parents is also being studied for the first time. We expect this study will increase knowledge of the effectiveness of this intervention in bringing immediate and sustained change in knowledge, behavior, toothbrushing habits, oral health, quality of life, and well-being in children aged 6 to 9 years and their parents. We aim to publish the results in a special edition of the International Dental Journal by March 2020. In addition, results will be presented at conferences and disseminated among project leaders as guidance for the development and continuation of implementation of school programs in their countries.

## Appendix

Multimedia Appendix 1

Multimedia Appendix 2 Child assent form—English.

Multimedia Appendix 3 Parent informed consent form—English.

Multimedia Appendix 4 Parent questionnaire—English.

Multimedia Appendix 5 Child questionnaire—English.

Multimedia Appendix 6 Decayed missing filled tooth index and simplified oral hygiene index: paper form for data collection.

## Abbreviations

AE: adverse event
BDN: Brush Day & Night
DMFT: Decayed, Missing, and Filled Teeth Index
FDI: FDI World Dental Federation
LSC: local study coordinator
OHI-S: Simplified Oral Hygiene Index
SAE: serious adverse event
T0: baseline
T0+21: end of 21-day intervention
T1: 8 weeks after the end of the intervention
T2: 24 weeks after the end of the intervention
